### Assignment of interventions: allocation

#### Sequence generation {16a}

Stratified block randomization will be used. Allocation tables were developed by KP in STATA 13.1 through the *ralloc* command using an allocation ratio of 1:1, randomly permuted blocks of varying sizes, and stratified by children’s age group (younger vs. older). We stratified by child's age group because the intervention will have separate sessions for younger and older children, as described in section "Intervention arm: Making Mindfulness Matter (M3)©".

#### Concealment mechanism {16b}

Randomization will be facilitated centrally through REDCap. The allocation sequence was generated and uploaded to REDCap by KP, who is not involved with participant recruitment, scheduling or any other forms of participant contact. This web-based system prevents circumvention of the randomization process and ensures allocation concealment.

#### Implementation {16c}

Randomization is stratified based on the child’s age group, as described in section “Sequence generation {16a}”. Randomization will occur as close as possible to the intervention to minimize the delay between study arm allocation and the delivery of the intervention. Therefore, once informed consent is received, the parent-child dyad will enter the queue for randomization. Given that the intervention will be delivered in groups of 4 to 8, and assuming some attrition and scheduling conflicts, once 12 to 16 participants per stratum are in queue for randomization and available for the scheduled date/time of the intervention, participants may begin the study by receiving the Baseline questionnaires (as described in the paragraph below). If there are controls who have completed the study and are in the queue to receive the intervention, at least 9 participants need to be in queue for randomization. This would ensure that a minimum of 4 participants are randomized to the control arm, which is important to fulfill our obligations to participants by providing all participants with the opportunity to receive the intervention. It would be ethically problematic if, for example, one participant is randomized and they are allocated to the control arm; this participant cannot be offered the intervention at the end of the study because at least 4 participants are needed to run the intervention sessions.

Once enough participants are ready to be randomized, those in the queue for randomization will receive an individualized link to the baseline questionnaire and electronic gift card via email 2 weeks before the first scheduled M3 session of the intervention arm. These participants will have 2 weeks to complete the questionnaire but will be asked to complete it within a week, to allow for a 1 week buffer. A member of the research team will also connect with the parent and child to attain assent of the child, complete the child Pre Assessment, and offer a short tutorial of how to use Zoom (the video conferencing application) if the parent is unfamiliar with this platform. Upon completion of the online baseline questionnaire by parents, the research coordinator will randomize participants via REDCap. Those randomized to the intervention (and controls who are in the queue for the intervention) will be provided with instructions on how access the online sessions. Those randomized to the control arm will be told that they will be placed in the next scheduled M3 sessions, after they complete the Immediate Follow-up questionnaire. Participants who were unable to complete the baseline questionnaire will be placed in the next scheduled group of participants to be randomized. After the M3 program is completed, the Research Coordinator will contact the family again to have the child complete the Post Assessment.

### Assignment of interventions: blinding

#### Who will be blinded {17a}

Blinding of participants and program facilitators (i.e., the staff delivering the M3 intervention) will be difficult given the nature of the intervention. However, blinding to study hypotheses will be achieved by explaining to participants and program facilitators that the study aims to evaluate the effectiveness of the intervention given to all participants; however, some participants will receive the intervention in the upcoming M3 session, whereas others will receive the next scheduled M3 sessions. In so doing, we hope to eliminate any biases associated with the participants’ and program facilitators’ perception or biases of being assigned to the intervention or control arm. The data analyst evaluating efficacy outcomes (e.g., HRQOL, mental health) will be blinded.

#### Procedure for unblinding if needed {17b}

There is no requirement for emergency unblinding procedures.

### Data collection and management

#### Plans for assessment and collection of outcomes {18a}

All data and questionnaires are captured online using REDCap. If needed, participants may request mailed questionnaires, which would be subsequently entered into REDCap by a member of the research team. Feasibility outcomes are collected throughout the course of the study (e.g., recruitment, randomization, retention, and the assessment procedures) by the research team. After each intervention session, the research assistant and facilitators will complete questionnaires on REDCap designed to assess adherence and quality of implementation. Facilitators will be emailed individualized links to the questionnaire through REDCap, whereas research assistants will be able to enter data directly on REDCap. On the day of an intervention session, participants will be emailed an individualized link through REDCap with the questionnaire they must complete before or at the start of the session and at the end of the session; these questions pertain to the content of the M3 sessions and their experience with the intervention.

Similarly, with respect to efficacy outcomes (Baseline, Immediate Follow-up, and Extended Follow-up questionnaire), participants will be emailed (through REDCap) an individualized link to the questionnaire along with an individualized link to a $25 gift card.

Individualized links will also be emailed through REDCap to clinicians who would complete a short questionnaire pertaining to the patient’s clinical characteristics.

#### Plans to promote participant retention and complete follow-up {18b}

If a session is missed, the research coordinator will contact the parent inquiring about the circumstances and identify if the trial investigators can provide any assistance to avoid missing future sessions. If randomized participants are not able to attend the M3 sessions, but would still be interested in completing the Immediate and/or Extended Follow-up questionnaires, they would be encouraged to do so. If participants withdraw, the reasons will be recorded and they will be presented with the option of completing the parent-reported QOLCE-16 [45, 46], an abbreviated version of the QOLCE-55, at the Immediate and/or Extended Follow-up, that is estimated to take less than 5 min to complete. This will be important to the intention-to-treat analysis in an attempt to follow all participants randomized into one of the two study arms.

#### Data management {19}

All data are entered onto REDCap [38], a widely utilized and secure web-based platform. The research team evaluating the quality of implementation and other study data undergo a 1.5-h training session and REDCap training. Data are held in a secure server at Lawson Health Research Institute, London, Ontario, Canada. REDCap is also utilized to randomize and email individualized questionnaire links to participants. Participants will not be required to provide an answer to each question. A number of quality control procedures in REDCap were specifically created for this project and will be utilized, such as providing participants with an ignorable warning that some questions have been left blank to minimize the frequency of missing questions. Other quality control procedures include providing warning or reminder messages to the research team (e.g., indicating that a participant is not eligible), preventing certain actions (e.g., preventing the randomization of participants unless all inclusion criteria are met and the Baseline questionnaire is completed), notifying the research team if adverse events are reported or if questions have been left blank, and tracking participants’ progression through the study and the time it took participants to complete each questionnaire. Once participants have completed their questionnaire, a research assistant will be notified by REDCap and subsequently review the responses and follow-up with participants if needed. If the participant requested paper questionnaires, the data will be reviewed and entered in REDCap by a research assistant.

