##### Primary outcome: feasibility

The primary objective of the trial, to evaluate the feasibility of implementing the intervention, will be assessed by evaluating (a) study procedures, (b) participant feedback and adherence to M3, and (c) intervention fidelity, as described below.

Study procedures will be evaluated by tracking (a) the number of patients contacted, (b) participating rate, (c) reasons and/or barriers for non-participation (such as the proportion of families without an internet connection and/or a computer/mobile device), (d) attrition, (e) participant burden (e.g., time to complete questionnaires), and (f) quality of questionnaire data (e.g., the proportion of missing data).

Participant feedback and adherence to M3 will be evaluated using three measures developed for this study (see the supplementary file). The first measure, the Weekly Parent Questionnaire, is completed online by parents at the start and end of each session. At the start of the session it asks about the utilization of M3 skills outside of the scheduled intervention sessions over the past week and whether any adverse events were experienced by the parent or child. At the end of each session, it asks about skills taught in that session and suggestions for improvement. The second measure, Parent Pre-Post Assessment, is completed online by parents at the start and end of the M3 program and evaluates understanding and utilization of the skills taught by M3, as well as participants’ satisfaction with the online program. The third measure, Child Pre-Post Assessment, is completed by children with the help of a research assistant through a video call prior to the first group session and after the program is completed. The measure evaluates children’s understanding of topics discussed in the group, such as how our brain works when we are upset and what mindfulness is. These questions will be read to the children by the researcher and are rated on a 3-point scale as indicated by a smiling, neutral and frowning face.

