##### Rationale for lack of child-reported measures

The majority of questionnaires will be completed by parents, with few exceptions (e.g., clinicians’ report on clinical characteristics, and children’s pre-post assessment of M3 skills). We acknowledge that children’s own perceptions are important and that this trial will not capture children’s perceptions of the intervention and its impact; however, we believe this is reasonable for three reasons. First and foremost, the primary objective of this pilot RCT is not to evaluate effectiveness as reported by children; the primary aim is to evaluate feasibility, focusing on participant adherence and facilitators’ adherence and quality of implementation. Second, questionnaires are completed at home and given the children’s age (4–10 years), parents would undoubtably have to provide the child with the questionnaires and likely assist, potentially biasing their responses. Lastly, given the children’s age (4–10 years), the choice of validated self-reported questionnaires is limited and it has been proposed that children under the age of 8 years may lack the cognitive maturity and verbal comprehension capacity to provide self-reports [61]. We are evaluating ways to best incorporate children’s self-reports in a subsequent large-scale RCT of M3.

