#### Participant timeline {13}

Parents will be able to complete all questionnaires online via REDCap, or if preferred, using mailed questionnaires. The baseline and follow-up questionnaires are estimated to take 90 min to complete. Parents will also be asked to complete a brief online questionnaire via REDCap at the start and end of each M3 session pertaining to the content of the M3 sessions and their experience with the intervention.

Figure 1 highlights participants’ progression through the study. Two weeks prior to the first M3 session of the intervention arm, participants will be sent the baseline questionnaire and asked to complete it within 1 week, which will allow for a 1-week buffer window prior to the first M3 session for the intervention arm. Once the Baseline questionnaire is completed, participants will be randomized. One week after the last M3 session for the intervention arm, all participants will be sent the Immediate Follow-up questionnaire. Participants will be asked to complete the questionnaire within 1 week, with the goal of receiving all completed questionnaires within 2 weeks.

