### Statistical methods

#### Statistical methods for primary and secondary outcomes {20a}

Descriptive statistics will be run with continuous variables summarized using means and standard deviations and categorical variables summarized using frequencies and proportions. To evaluate study feasibility, descriptive statistics will be used to summarize study procedures among all participants, including (a) number of families contacted, (b) participation rate, (c) reasons and/or barriers for non-participation, (d) attrition rate, (e) time to complete questionnaires, and (f) missing data on questionnaires. To evaluate (1) participant feedback and adherence to M3 and (2) intervention fidelity, data from the intervention and control arms will be combined and descriptive statistics used to describe responses to the Weekly Parent Questionnaire, Parent Pre-Post Assessment, and Child Pre-Post Assessment, M3 Adherence Checklist, and Quality of Implementation questionnaire.

To evaluate Efficacy Outcomes (e.g., HRQOL), we will use linear mixed models, which are suitable for group-administered interventions to account for the clustering in the intervention arm and no clustering in the control arm [63, 64]. The primary interest will be comparing the mean scores of the intervention and control arms at the Immediate Follow-up (e.g., HRQOL 1-week post-M3), adjusting for potential imbalance at Baseline (e.g., HRQOL pre-M3). Given that age group (younger vs. older) was a variable used in stratifying randomization, analyses will adjust for age group.

Similarly, generalized linear mixed models will be used to evaluate whether the intervention and control arms differ with respect to the proportion who show clinically significant improvement, and the proportion with clinically elevated symptoms post-intervention [65].

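### Questionnaire completion time, a component of the primary feasibility outcome, falls under a mean-and-SD rule that a few long interruptions could distort; a median and interquartile range would be safer

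*Protocol article*

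**What the plan says.** Objectives {7} gives completion time as an example of the study procedures to be evaluated under the primary objective. The section on the primary outcome, within Outcomes {12}, repeats it as "participant burden (e.g., time to complete questionnaires", item (e) of six study-procedure measures.

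The source of the measurement is in Data management {19}: REDCap tracks "the time it took participants to complete each questionnaire". The summary is in Statistical methods {20a}, which opens with "Descriptive statistics will be run with continuous variables summarized using means and standard deviations" and then lists "e) time to complete questionnaires" among the feasibility items to be described. It names no median, quartiles or range for this variable, and no handling of interrupted sessions or paper forms.

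Three other passages describe how the forms are filled in:

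- Participant timeline {13}: "The baseline and follow-up questionnaires are estimated to take 90 min to complete".
- Rationale for lack of child-reported measures: "questionnaires are completed at home".
- Implementation {16c}, on the baseline form: "These participants will have 2 weeks to complete the questionnaire but will be asked to complete it within a week".

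Parents may ask for mailed questionnaires instead, which staff later enter into REDCap (Plans for assessment and collection of outcomes {18a}; Data management {19}).

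**The concern.** Completion times cannot fall below zero and have no natural upper limit, so they tend to be right-skewed even under supervision. Here the form is long, it is done at home, and the respondents are parents of children aged 4 to 10. Some interruption is plausible. If the system's clock keeps running while a parent is away, a single overnight gap adds many times the working time to that parent's record. The mean and SD would then partly describe gaps rather than effort.

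Mailed forms raise a separate point that does not depend on how the clock works. REDCap cannot observe how long a parent spent on paper, and the article does not say how such forms enter the burden figure.

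What is at stake is modest: one descriptive estimate of burden, which Objectives {7} says will help prepare the multi-centre trial.

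**Working it through.** **Inputs from the article.** Expected time 90 min (Participant timeline {13}). Planned recruitment 100 dyads with 24% attrition allowed (Sample size {14}); 100 × (1 − 0.24) = 76, the 2 × 38 dyads required. The 90 minutes is a planning estimate without stated components, so it cannot be reproduced.

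**Assumptions, not in the article.** Uninterrupted time has mean 90 and SD 20 min. The tracked time is elapsed time. Of N parents, k pause once for P minutes.

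**Formulas.**

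- Mean = 90 + kP/N
- SD = √[ k(N − k)P² / (N(N − 1)) + 20² ]

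**Three 24-hour pauses, N = 100** (P = 1440):

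- Mean = 90 + 3 × 1440/100 = 133.2 min
- SD = √[ 3 × 97 × 1440² / (100 × 99) + 400 ] = √(60,951 + 400) = 247.7 min

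**Three 3-hour pauses, N = 100** (P = 180):

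- Mean = 90 + 3 × 180/100 = 95.4 min
- SD = √[ 3 × 97 × 180² / (100 × 99) + 400 ] = √(952 + 400) = 36.8 min

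**Other cases by the same formulas:**

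| N | Parents pausing | Pause | Mean (min) | SD (min) |
|---|---|---|---|---|
| 100 | 0 | none | 90 | 20 |
| 100 | 3 | 3 h | 95 | 37 |
| 100 | 1 | 24 h | 104 | 145 |
| 100 | 3 | 24 h | 133 | 248 |
| 100 | 3 | 72 h | 220 | 741 |
| 76 | 3 | 24 h | 147 | 283 |

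**Median.** With 3 of 100 records moved to the far right, the median m solves 0.97 × F(m) = 0.5, so F(m) = 0.5155. If uninterrupted times are roughly normal, m = 90 + 0.039 × 20 ≈ 90.8 min. This holds for any pause long enough to carry those three records well above 90, so the median is about 90 in both the 3-hour and the 24-hour case.

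**Skew without pauses.** If working time is instead lognormal with mean 90 and SD 30 (also an assumption), the median is 90/√(1 + (30/90)²) = 85 min. Ordinary skew alone separates mean and median by about 5 minutes. A large distortion needs long interruptions and a clock that counts them.

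**The case against.** The strongest objection is that the harm rests on a system setting the article does not describe. It does not say whether the tracked time is elapsed or active, or whether a form can be left and resumed. The baseline window of up to 2 weeks runs from sending the link, not from opening the form, so it does not show that forms stay open. If times are logged separately for each instrument, gaps between instruments may not count. All of this stands, and it makes the size of the distortion conditional.

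A second objection is that the opening sentence of {20a} is standard wording for all continuous variables. The feasibility sentence promises only descriptive statistics, and nothing forbids adding a median. That stands in part: this is no contradiction or error. But "continuous variables summarized using means and standard deviations" is the only summary the article states for a continuous measure, and completion time is listed in the same paragraph. The weaker statistic is therefore written in, not merely left open.

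Third, the distortion would show itself, because an SD of 248 beside a mean of 133 alerts any reader. True, but the reader would then know that the figure is unreliable without having a usable one.

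Some stronger readings are tempting. A reader might infer that burden will be reported at several times its real value, that observed time is to be judged against 90 minutes or compared between time points, or that instruments might be dropped as a result. The article supports none of these. It gives no pausing rate or pause length, plans no such comparison and ties no progression rule to the figure. Attrition and missing data, which also bear on burden, are reported separately.

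**Conclusion.** The point holds as a minor weakness in the choice of summary. The article places a time that is likely to be right-skewed, recorded by the system and unsupervised, under a mean-and-SD rule, although the time is a component of the primary feasibility outcome.

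Under elapsed-time tracking and an assumed uninterrupted 90 (SD 20) min, three day-long pauses among 100 parents raise the mean by 43 minutes and multiply the SD about twelvefold (248/20). Three 3-hour pauses raise the mean by about 5 minutes and not quite double the SD (37/20). Only the 90 minutes and the 100 dyads come from the article; the SD, the number of pauses and their length are illustrative. If tracking counts active time only, what remains is ordinary skew and the unaddressed paper forms.

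No test, sample size or go/no-go decision is affected. The consequence is limited to a descriptive estimate carried into planning the next trial.

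**What to change.** In {20a}, state that completion time will be reported as median and interquartile range, with the range, in place of or alongside mean and SD. Base it on forms completed online, and give the number completed on paper.

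Do not drop times above a fixed limit from the main summary. A cut-off would also remove parents who are genuinely slow, for whom the burden is greatest, and so bias the estimate downward. The median already protects against a few long pauses. A summary restricted in that way can be shown, at most, as a secondary description.

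The cost is one added line of reporting. It needs no new data and leaves every other analysis unchanged. If the tracked time proves to be active time, nothing is lost.

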#### Confidentiality {27}

REDCap servers follow hospital security guidelines and policies and all the web-based information transmission is encrypted. REDCap was developed specifically around Health Insurance Portability and Accountability Act (HIPAA)-Security guidelines and is recommended to researchers by Privacy Offices and Institutional Review Boards of many organizations.

#### Plans for collection, laboratory evaluation, and storage of biological specimens for genetic or molecular analysis in this trial/future use {33}

No biological samples will be collected.

### Statistical methods

#### Statistical methods for primary and secondary outcomes {20a}

Descriptive statistics will be run with continuous variables summarized using means and standard deviations and categorical variables summarized using frequencies and proportions. To evaluate study feasibility, descriptive statistics will be used to summarize study procedures among all participants, including (a) number of families contacted, (b) participation rate, (c) reasons and/or barriers for non-participation, (d) attrition rate, (e) time to complete questionnaires, and (f) missing data on questionnaires. To evaluate (1) participant feedback and adherence to M3 and (2) intervention fidelity, data from the intervention and control arms will be combined and descriptive statistics used to describe responses to the Weekly Parent Questionnaire, Parent Pre-Post Assessment, and Child Pre-Post Assessment, M3 Adherence Checklist, and Quality of Implementation questionnaire.

To evaluate Efficacy Outcomes (e.g., HRQOL), we will use linear mixed models, which are suitable for group-administered interventions to account for the clustering in the intervention arm and no clustering in the control arm [63, 64]. The primary interest will be comparing the mean scores of the intervention and control arms at the Immediate Follow-up (e.g., HRQOL 1-week post-M3), adjusting for potential imbalance at Baseline (e.g., HRQOL pre-M3). Given that age group (younger vs. older) was a variable used in stratifying randomization, analyses will adjust for age group.

Similarly, generalized linear mixed models will be used to evaluate whether the intervention and control arms differ with respect to the proportion who show clinically significant improvement, and the proportion with clinically elevated symptoms post-intervention [65].

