##### Control arm: waitlist control

Child-parent dyads randomized to the control arm will continue treatment as usual. They will complete the baseline and immediate follow-up questionnaire at comparable times to families in the intervention arm; they will not complete the Extended Follow-up questionnaire. These dyads will be provided with the intervention at the next scheduled session after they have completed the immediate follow-up; the goal is to provide the intervention to controls as soon as possible to avoid differential attrition between the intervention and control arm. During the intervention sessions, participants in the control arm will complete all feasibility questionnaires before and after each session, pertaining to the intervention and their satisfaction with each session.

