##### Explanation for the choice of comparators {6b}

Attention placebo control (APC) is preferable over treatment as usual or waitlist control for psychological interventions, to account for non-specific effects a group setting may offer such as social support/social attention [39]. However this design is rarely used in such trials [40]. Two key challenges may explain why the theoretical benefits of APCs have not been realized in practice and informed our decision to not use an APC in this current trial: (1) Disproportional drop-out has been documented; a study assessing a parent training program reported 18% and 50% attrition in the intervention and APC arms, respectively [40]. Furthermore, the reasons for drop-out were different; parents in the APC dropped out without reason or indicating a preference to be in the intervention rather than the APC arm, while parents in the intervention arm dropped out due to scheduling issues. (2) Potential for an ethical issue in a APC arm where participants’ comments and questions in discussions show a risky misunderstanding of key topics related to parenting, which should be addressed but where doing so is outside the protocol for the undirected discussion condition of the APC [40]. We view both these challenges as very likely to occur in the epilepsy population. Given that the aim of the current pilot trial is to evaluate feasibility, we will utilize a waitlist control arm and provide controls with the intervention as soon as possible, to avoid differential attrition between the intervention and control arm. For the subsequent full RCT, we are exploring possible programs to utilize as APC and are considering a cluster random allocation process where all the eligible participants recruited from each institution would be randomized as a group (cluster) to either the intervention or an APC arm where it is much easier to ensure blinding of participants to reduce the likelihood of uneven drop-out. Additionally, a specific a priori protocol could be developed for the APC to incorporate strategies for addressing misinformation about epilepsy.

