**Fig. 1 Fig1:**
[figure not shown]
Schematic of participant progress

Participants in the intervention arm will be asked to complete a similar questionnaire, the Extended Follow-up, 10 weeks after the end of the M3 session. For participants in the control arm, the Immediate Follow-up questionnaire is the final follow-up questionnaire they complete. To provide interested controls with the intervention as soon as possible, those interested in receiving the intervention will be placed in a queue and will be able to join the next scheduled M3 sessions. Therefore, M3 sessions may be composed of participants randomized to the intervention arm and/or controls who have completed the study (completed Baseline and Immediate Follow-up questionnaires). During the M3 sessions, all participants will complete the same online questionnaires pertaining to the content of the M3 sessions and their experience with the intervention. Once the intervention ends, those who were randomized to the control arm will not need to complete any follow-up questionnaires. Therefore, the role of the controls in the intervention would be to simply honor the commitment for everyone to receive the M3 sessions and to “fill” the group (given that 4–8 participants are needed per group). The advantage of including dyads randomized to intervention and dyads previously randomized to the control arm is that it will increase the pool of participants waiting to receive the intervention and thereby expedite the time it takes to fill each group. The other advantage is that it would ensure that dyads randomized to the control group will receive the intervention as soon as possible and ameliorate attrition in the control group.

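### Adherence to and feedback on M3, part of the primary feasibility outcome, are summarised only over both arms combined, mixing dyads randomised to M3 with controls selected after randomisation

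*Protocol article*

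**What the plan says.** The Objectives and Outcomes {12} sections make feasibility the primary objective, with three components: study procedures, participant feedback and adherence to M3, and intervention fidelity. Statistical methods {20a} treats these in two sentences.

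- Study procedures, including attrition and missing questionnaire data: "descriptive statistics will be used to summarize study procedures among all participants".
- Feedback, adherence and fidelity: "data from the intervention and control arms will be combined and descriptive statistics used to describe responses to the Weekly Parent Questionnaire", followed by the Parent and Child Pre-Post Assessments and the two fidelity forms.

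No separate summary for dyads randomised to M3 is stated for the second set.

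Three statements determine which controls contribute.

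- Participant timeline {13}, on interest: "those interested in receiving the intervention will be placed in a queue and will be able to join the next scheduled M3 sessions".
- Participant timeline {13}, on completion: "M3 sessions may be composed of participants randomized to the intervention arm and/or controls who have completed the study".
- The control arm section, on data: "participants in the control arm will complete all feasibility questionnaires before and after each session".

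The timeline section also says that "the role of the controls in the intervention would be to simply honor the commitment for everyone to receive the M3 sessions". Their only other stated purpose there is making up group numbers.

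**The concern.** A control dyad appears in the adherence and feedback data only after it has stayed through the Immediate Follow-up and, on the timeline's wording, expressed interest. Controls who withdrew or lost interest while waiting are absent. Dyads allocated to M3 start without that filter, so early disengagement among them remains part of the picture. Pooling the two gives a figure for neither the M3 arm as randomised nor the control arm as randomised.

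The protocol also sits uneasily with itself. It describes controls in M3 as there to honour a promise and fill places, yet gives their responses the same standing as those of randomised M3 dyads in a primary-outcome component.

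This matters because the Objectives and Discussion sections say that the results will prepare a larger multicentre trial. That trial needs to know how families behave when allocated to M3. A figure raised by a retained, interested subgroup would lead its planners to expect better adherence than they will get.

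**Working it through.** **1. Inputs from the protocol.** The planned total is 100 dyads, randomised 1:1, so 50 per arm. Planned attrition is 24%. The document gives no adherence rate, so there is no plan figure for adherence to reproduce.

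**2. Check of the sample-size figures used here.** Per arm without clustering: 2 × (1.96 + 0.84)² / 0.8² = 24.5, so 25. With the stated ICC of 0.10 and group size of 6, the design effect is 1 + (6 − 1) × 0.10 = 1.5, and 25 × 1.5 = 37.5, so 38 per arm. Then 76 / (1 − 0.24) = 100. The stated 38 and 100 reproduce. At the planned attrition, 50 × 0.76 = 38 controls would complete the Immediate Follow-up and could enter M3. A few not taking it up would leave about 35 (assumed).

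**3. Effect of pooling on adherence.** With n₁ randomised M3 dyads adhering at rate p₁ and n₂ waitlist recipients at rate p₂, the pooled rate is (n₁p₁ + n₂p₂) / (n₁ + n₂). It departs from p₁ by (p₂ − p₁) × n₂ / (n₁ + n₂). All adherence rates below are assumptions, with n₁ = 50 and p₁ = 70%:

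| n₂ | p₂ | Pooled rate | Shift from 70% (points) |
|---|---|---|---|
| 35 | 85% | (35 + 29.75) / 85 = 76.2% | +6.2 |
| 38 | 85% | (35 + 32.3) / 88 = 76.5% | +6.5 |
| 35 | 90% | (35 + 31.5) / 85 = 78.2% | +8.2 |
| 38 | 90% | (35 + 34.2) / 88 = 78.6% | +8.6 |
| 38 | 70% | (35 + 26.6) / 88 = 70.0% | 0 |
| 38 | 60% | (35 + 22.8) / 88 = 65.7% | −4.3 |

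The shift is zero when the rates are equal and negative if controls adhere less well after their wait. With 38 controls, they carry 38 / 88 = 43% of the weight.

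**4. What can be separated by arm.** The Weekly Parent Questionnaire and the Pre-Post Assessments are completed per parent or child, so they can be split by allocation. The M3 Adherence Checklist and the Quality of Implementation form are completed per session by facilitators and research assistants. Because a session may contain both arms, these two cannot be split.

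**5. Attrition.** A single overall rate cannot by itself show whether the arms differ. With 50 per arm, an overall 24% fits 24%/24% (38 and 38 completers), 18%/30% (41 and 35), 10%/38% (45 and 31) or 0%/48% (50 and 26). This is a reason to show attrition by arm. It is not evidence that the protocol intends otherwise.

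**The case against.** **Describing everyone who received M3 is legitimate.** All recipients get the same standardised programme and complete the same session questionnaires, and the aim is to learn whether M3 can be delivered. This stands, and it is why the pooled figure should remain as a secondary display. It does not supply the missing summary for dyads randomised to M3.

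**The direction of any bias is not certain.** Every dyad must be willing at enrolment to attend all sessions. Controls join a later schedule after waiting, which could lower their adherence. The control arm and Implementation {16c} sections also read as if all controls who complete follow-up are placed in M3, so the interest filter may be weak. This stands too: an upward shift is plausible, not demonstrated.

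**A reader might infer that the plan hides differential attrition.** The control arm section says "the goal is to provide the intervention to controls as soon as possible to avoid differential attrition between the intervention and control arm", and attrition is summarised over all participants. The document does not support that inference. Attrition is in a different sentence from the one that combines arms, and that sentence names a population without ruling out tables by arm. Its list opens with families contacted and participation, which precede randomisation. Flow by arm is routinely left to the analysis plan or trial report. The protocol does report that "a study assessing a parent training program reported 18% and 50% attrition in the intervention and APC arms, respectively", but this concerns an attention-placebo comparator in another study and says nothing about what to expect in this waitlist trial.

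**A reader might also infer that all primary feasibility outcomes are wrongly pooled.** They are not. Fidelity is recorded per session and has to be pooled.

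**Conclusion.** The point holds for participant feedback and adherence. The protocol fixes a combined-arm summary for a primary-outcome component, the control contributors are selected after randomisation, and no summary for dyads as randomised to M3 is stated. Under the assumed rates of 70% against 85% to 90%, the overstatement is 6.2 to 8.6 points. The true size and direction are unknown, and equal rates give none.

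This is a reporting weakness that can be corrected from data already collected. It does not threaten the randomised comparison, and it changes no efficacy estimate, error rate or sample size. For attrition and missing data, only a clarification is warranted.

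**What to change.** In Statistical methods {20a}:

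- Make dyads randomised to M3 the lead summary for adherence (attendance and use of skills) and for feedback. Attendance is already tracked under Strategies to improve adherence {11c}; use all dyads randomised to M3 as its denominator.
- For questionnaire items, including reported skill use, use responders as the denominator and state how many of the randomised dyads responded. Dyads who never attend give no session feedback, so an all-randomised denominator cannot work for these items.
- Show waitlist recipients in a separate column, with the numbers eligible for M3, accepting it and starting it. Give the pooled figure as a secondary display.
- Keep session-level fidelity pooled.
- As a clarification, state that attrition and missing data will be shown by arm at the Immediate Follow-up. That is the only follow-up both arms share, because controls do not complete the Extended Follow-up.

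The cost is wording and table layout, since randomisation and the questionnaires are both handled in REDCap. The lead adherence figure loses some precision. At an assumed 70%, the simple 95% half-width is 1.96 × √(0.70 × 0.30 / 50) = 12.7 points with 50 dyads, against 1.96 × √(0.70 × 0.30 / 88) = 9.6 points with 88, ignoring clustering within groups.
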